### Statistical and analytical plan

To evaluate the effect of each individual cycle of CFZ+BELA on cPRA, we will fit a linear mixed model with the patient treated as a random effect to control for repeated measures from the same patient. Continuous data (MFI) will be evaluated by mean MFI for class I and class II antibodies respectively with significance determined using student’s T-test. Net MFI reduction will be calculated as: (pre-treatment mean MFI – post treatment mean MFI) / pre-treatment mean MFI. Descriptive statistics in the form of means and standard deviations or medians and inter-quartile ranges will be calculated before and after desensitization cycles for all antibody titers of interest and cPRA. Multivariable analyses of covariance will examine changes in antibody titers and cPRA after controlling for a limited number of clinically important covariates. Paired t-tests or Wilcoxon Signed Rank tests will also be used to examine whether levels of antibody titers and cPRA remain constant between the last desensitization cycle and time of transplant, and to assess reductions in DSA.

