**Plasmapheresis**		
Removes circulating immunoglobulins via extracorporeal plasma antibody filtration.	Often used alongside IVIG, has been shown to reduce PRA in some heart transplant candidates through outcomes vary by antibody burden and patient factors.	Antibody rebound due to rapid diffusion from extravascular space can occur and multiple treatments are usually needed to achieve low circulating antibody levels.

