## Carfilzomib and belatacept

Desensitization therapies as discussed above, generally deplete or modulate antibodies or affect B-cell activity without affecting antibody production by plasma cells. Proteosome inhibitors (PIs) induce apoptosis in response to the accumulation of misfolded proteins. The high rate of immunoglobulin synthesis by antibody secreting cells (ASCs) underlies their susceptibility to PI-based therapies. Carfilzomib (CFZ) is a 2nd generation, irreversible inhibitor of 20S proteasomal subunit. CFZ causes less neuropathy than its first-generation cousin bortezomib and may have less antibody rebound due to its irreversible binding^11^. CFZ as desensitization monotherapy in renal transplant patients led to a reduction in HLA antibodies and in bone marrow plasma cells (BMPCs) with acceptable drug safety and toxicity^16^. In HT candidates, desensitization with CFZ, plasmapheresis and IVIG led to a decrease in cPRA from 76% to 40%. A rejection episode was documented in a patient with C1q-PRA of 54% suggesting a limitation in more highly sensitized candidates^15^. From a mechanistic standpoint, bone marrow CD138+ plasma cells (PCs) secrete antibodies with specificities that mirror those in peripheral blood – underscoring their contribution to HLA sensitization. CFZ reduces CD138+ BMPCs by ≥ 50%, including the HLA repertoire in sensitized patients^17^. However, the *response is incomplete* and accompanied by brisk rebound following treatment completion^16^. While several factors are thought to contribute, homeostatic proliferation in germinal centers (GCs) is thought to drive repopulation^18^, highlighting the contribution of memory B cells, which can enter the GC leading to robust recall responses. These observations argue for combinatorial therapies targeting not only the PC compartment but also GCs and memory B cells.

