#### Primary aim

Study the efficacy and effectiveness of our proposed combined protocol with CFZ and BELA. We will investigate whether each cycle of desensitization is effective at.

i) reducing antibody strength as measured by MFI and titers and.

ii) lowering the calculated panel reactive antibody (cPRA).

We hypothesize that this protocol will lead to a meaningful decrease in antibody strength, with stepwise dilution of serum demonstrating gradual elimination or decrease in MFI such that the corresponding antigens would no longer be considered unacceptable. This would lower the cPRA, thereby allowing the use of a greater donor population. We will also determine whether the reduction in antibody strength is maintained with BELA between the last cycle and time of transplant. Reduction in DSA at the time of crossmatch will be studied to establish the functional relevance of our strategy. Sensitizing events defined per CTOT criteria^3^, as well as clinical events associated with the use of the proposed protocol will be monitored.

#### Secondary aim 1

Determine how desensitization impacts cellular subsets responsible for circulating anti-HLA antibodies. Using a series of state-of-the art techniques, we will combine global approaches (multiparameter flow, transcriptomics) with studies to delineate antigen specific responses (allo and viral) together establishing how desensitization shapes the B- and T-cell compartment and determine whether the response is sustained under BELA.

#### Secondary aim 2

Assess waitlist mortality and post-transplant outcomes using the Pediatric Heart Transplant Society (PHTS) database. We hypothesize that mortality before and after transplant will be comparable to overall PHTS outcomes^5^, both with and without positive crossmatch. Crossmatch (XM) status at the time of transplant will be recorded for each patient, and patients will be followed for at least one year after transplant to assess for antibody mediated rejection (AMR), ISHLT grade acute cellular rejection ≥2R (ACR), cardiovascular mortality, or need for retransplantation. While the primary analysis will focus on the first post-transplant year to align with available PHTS data, we anticipate extending this work in the future to evaluate longer term outcomes as data maturity allows.

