### Study regimen

The desensitization protocol is a combination of CFZ and BELA to be given every week for 4 weeks as part of one cycle (Figure 2). CFZ 20 mg/m^2^ IV on day 1, 27mg/m^2^ on day 2, and 36 mg/m^2^ on days 8, 9, 15, and 16. Patients will receive pre-medication with acetaminophen, diphenhydramine, methylprednisolone and ondansetron to minimize side effects. Patients will also be pre-hydrated with 500 ml normal saline prior to CFZ based on clinical status. BELA 10 mg/kg on days 1, 8, 15, and 28, and q28 days after first cycle; to be infused over 30 min using a 0.2-to-1.2-micron low protein binding filter. We anticipate that a number of patients will need multiple cycles in order to have sequential reduction in antibodies and to increase the likelihood of finding a donor. Once patients are deemed to be adequately desensitized (see Antibody evaluation), they will be maintained on monthly BELA (10 mg/kg) until the time of transplant. Following cycle 1, centers can choose to augment therapy (for example, with plasmapheresis) based on their established desensitization protocols and clinical judgment.

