### Antibody evaluation

We will collect samples pre and post each cycle to assess for any change in class I and class II anti-HLA abs (MFIs, titer and cPRA). They will also be collected at two-week intervals during the maintenance phase. Serum samples will be sent to, logged, processed, and stored at the HLA core ([name]). Serum samples will be aliquoted in multiple vials to minimize the need of freezing and thawing. Per manufacturer’s instructions, LS1A/LS2A tests will be performed for single-antigen bead (SAB) analysis on the LuminexTM system (One Lambda Thermo Fisher, Canoga Park, CA). The reactions of a given anti-HLA specificity will be expressed as MFI. The drawbacks of using cPRA based on neat MFI values is that i) it only provides a semi-quantitative measure of alloantibody that is impacted by inherent assay limitation and laboratory variability and ii) partial therapeutic effects can be missed because reduction in antibody quantity without completely removing it does not translate to a change in cPRA. One way to overcome these weaknesses is by performing serum dilutions to determine antibody titer and establish the cPRA at various titers. Stepwise dilution of the serum will gradually eliminate antibody positivity and thus decrease the cPRA because the corresponding antigens would no longer be considered unacceptable^7^. We expect that this approach will help stratify patients prior to inclusion in studies and assist in discerning partial therapeutic effects. Titration of serum pre-testing will be performed (1:4, 1:16, 1:64 dilutions) and re-tested for antibody specificity on SAB analysis. We will evaluate the cPRA at different time points and at different dilutions to determine significant changes. A meaningful response following the cycles of treatment will be defined in two ways:i)cPRA < 50% using an MFI threshold ≥ 4000 based on previous data^15^ orii)50% reduction in MFI and a 2-log reduction in titer as recommended by the Sensitization in Transplantation: Assessment of Risk (STAR) 2022 Working Group^6^.

Antibody evaluation done at the core lab will not be used for clinical decision making at the study sites; those decisions will be made based on antibody evaluations from the HLA laboratories of the individual sites, per their routine practice.

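### From cycle 2 on, the per-cycle estimate labelled as the effect of CFZ+BELA also contains whatever therapy the site added

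*Protocol article*

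**What the plan says.** The Primary aim section puts the question per cycle: "We will investigate whether each cycle of desensitization is effective at" reducing antibody strength and lowering cPRA. The Statistical and analytical plan answers it with a model for the "effect of each individual cycle of CFZ+BELA on cPRA, we will fit a linear mixed model with the patient treated as a random effect". That sentence names no term for other therapy. A separate analysis of covariance is planned, with covariates not named.

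The Study regimen section describes what patients receive. On added therapy: "Following cycle 1, centers can choose to augment therapy (for example, with plasmapheresis) based on their established desensitization protocols and clinical judgment". On stopping: "Once patients are deemed to be adequately desensitized (see Antibody evaluation), they will be maintained on monthly BELA". Further cycles thus go to patients not yet judged adequately desensitized.

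The Antibody evaluation section supplies the data: "We will collect samples pre and post each cycle to assess for any change in class I and class II anti-HLA abs". Table 1 describes plasmapheresis as filtering immunoglobulin out of the circulation, and adds that "Antibody rebound due to rapid diffusion from extravascular space can occur".

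**The concern.** The label on the estimate and the treatment behind it agree in cycle 1 and part company after it. Plasmapheresis lowers circulating antibody whether or not CFZ+BELA is working. A later cycle in which CFZ+BELA contributes nothing could therefore be reported as effective.

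Adjustment cannot be relied on to undo this. Augmentation is not offered before cycle 2, it is the site's choice, and it plausibly goes to the patients responding least.

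The sample size section says the results will inform effect sizes for a larger study, so a drop credited to the wrong therapy would carry over into that design. The Limitations section mentions varying induction and maintenance immunosuppression but not augmentation during desensitization.

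**Working it through.** **The plan's own figure.** The sample size section claims 80% power at d = 0.53 for a paired t-test with 30 patients. With a two-sided 5% level (assumed; not stated), the noncentral t with 29 degrees of freedom gives 80.1%. The figure reproduces and is not in dispute.

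**Inputs.** From the article: 30 patients and the cPRA cut-off of 50%. Assumed, because the article gives none of them: the share augmented, the extra drop, assay SD 5, between-patient response SD 0 to 8, and 25 patients reaching cycle 2. A cycle's effect is taken as pre-cycle minus post-cycle cPRA, so drops are positive.

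**Step 1: size of the bias.** If a share p of the patients in a cycle have sessions during it, and these lower cPRA by a further x points:

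- estimate = CFZ+BELA effect + p·x
- p = 0.5, x = 5: bias 2.5 points
- p = 0.5, x = 10: bias 5 points
- p = 0.5, x = 15: bias 7.5 points

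**Step 2: check by simulation.** A mixed model with a random patient intercept and a separate pre/post term per cycle was fitted to simulated data with a true drop of 15 points per cycle. Everyone received three cycles.

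| Scenario | Cycle 1 | Cycle 2 | Cycle 3 |
|---|---|---|---|
| No augmentation | 14.8 | 14.9 | 14.7 |
| Half augmented, 10 points | 14.9 | 19.9 | 19.8 |

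The later cycles shift by about 5 points, as Step 1 predicts; cycle 1 does not move. A second simulation added response-driven stopping (response SD 8). It gave a cycle 2 estimate of 18.6 against a true CFZ+BELA effect of 13.6 in the patients treated, again 5 points.

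**Step 3: timing can reverse the sign.** Suppose sessions fall just before the pre-cycle sample and 10 points rebound by the post-cycle sample in half the patients. The cycle 2 estimate becomes 13.6 − 0.5 x 10 = 8.6, so the cycle looks weaker than it is.

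**Step 4: false attribution.** Let CFZ+BELA have zero mean effect in cycle 2, with n = 25.

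- Variance of a patient's change = 2·5² + p(1−p)x² + (response SD)²
- Noncentrality = p·x / (SD of change / √25)

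| p, x | Response SD | SD of change | Noncentrality | Chance of a significant drop |
|---|---|---|---|---|
| 0.5, 10 | 0 | √75 = 8.66 | 5/1.73 = 2.89 | 79% (simulated 78%) |
| 0.5, 10 | 8 | √139 = 11.79 | 5/2.36 = 2.12 | 53% |
| 0.5, 5 | 0 | √56.25 = 7.50 | 2.5/1.50 = 1.67 | 36% |
| 0.5, 5 | 8 | √120.25 = 10.97 | 2.5/2.19 = 1.14 | 19% |

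Without augmentation the chance is 2.5% by construction.

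**Step 5: selection into later cycles.** With stopping at site cPRA below 50 and no augmentation, the model of Step 2 gives 15.1/12.5/7.9 for cycles 1/2/3 when response varies between patients (SD 10), and 15.1/15.1/15.0 when it does not. In the second simulation, the selection-only within-cycle estimates lay within 0.1 of the true effect in the patients who received that cycle. Selection changes whom the estimate describes; it does not bias the within-cycle effect.

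**The case against.** The strongest reply is that the protocol as delivered is the target. The Primary aim section speaks of efficacy and effectiveness of the combined protocol, optional augmentation is written into the regimen, and the study is observational. That is a legitimate estimand, and the fix keeps it. It is not what the statistical plan's sentence says, which attributes each cycle's effect to CFZ+BELA.

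A second reply is that a full protocol or analysis plan may record augmentation and adjust for it. It may, and unnamed covariates are no fault in an article. The point rests on the label the article fixes, which its own regimen contradicts. Figure 2, which may show sampling times, was not available, so the direction of the bias cannot be settled.

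Third, the sizes are assumed. The Antibody evaluation section itself warns that partial antibody reduction may leave neat cPRA unchanged. If plasmapheresis does not move cPRA, the bias in cPRA is nil. This stands as a limit on the magnitude.

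Three stronger readings are tempting and not supported:

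- **Selection as bias.** A reader might infer that stopping on response invalidates the later-cycle estimates. Step 5 shows otherwise, and the article plans no comparison of cycle 1 with cycle 3 that changing patient mix would distort.
- **Cycle 1 as a clean causal estimate.** Cycle 1 precedes permitted augmentation, but there is no control group. If the qualifying cPRA also serves as the pre-cycle value, regression to the mean alone could give an apparent drop of about 0.3 to 4.9 points (assumed population mean 40 to 75, SD 20, assay SD 5 to 10).
- **The response definition as mislabelled.** It refers to response after the treatment cycles and does not credit CFZ+BELA alone.

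**Conclusion.** The point holds as a mismatch between label and treatment from cycle 2 on. Followed as written, the plan credits CFZ+BELA with any change produced by site-chosen therapy. For sessions within a cycle, the bias equals the share augmented times the extra drop; that arithmetic needs only additivity. Its value is unknown because the article gives neither quantity: 2.5 to 7.5 cPRA points with half augmented and 5 to 15 points extra, and the opposite sign if sessions precede the pre-cycle sample and antibody rebounds. The chances of a falsely attributed drop (53 to 78%, or 19 to 36%) depend on the assumed response SD as well as on p, x, assay SD and 25 patients in cycle 2. They illustrate the risk and do not predict it. The matter deserves correction because per-cycle effectiveness is the primary aim and the change is cheap.

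**What to change.** In the Statistical and analytical plan:

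1. Name the cycle 1 pre/post change as the per-cycle estimate free of protocol-permitted augmentation, and say that it is uncontrolled and open to regression to the mean.
2. Record the type and dates of any augmentation relative to the pre- and post-cycle samples.
3. Report the change in cycle 2 onward separately for augmented and non-augmented cycles, as descriptive, and state that it applies to patients who needed that cycle.
4. Label pooled later-cycle results and the baseline-to-last-cycle change as the effect of the strategy including site augmentation.

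The cost is analysis wording and two data fields that sites should already hold. No samples, patients or limits on clinical care are added. The downside is that the split in step 3 is not randomized and the groups are small: with about 25 patients in cycle 2 and half augmented, roughly 12 in each, and fewer in cycle 3. Claims about later cycles become descriptive.

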### Number of subjects and sample size justification

A cohort of 30 patients across the 6 clinical sites during the 4-year study period is fixed by the limited population of patients meeting eligibility criteria for the study. This study is preliminary and results from the current work will be used to inform reasonable effect sizes when calculating power and sample sizes for a larger-scale study. With a cohort of 30 patients, we will have 80% power to detect moderate standardized effect sizes of Cohen’s d = 0.53 for analyses using paired t-tests and Cohen’s d=0.55 for analyses using Wilcoxon Signed Rank tests (Aim 1). We will also have 80% power to detect a large Chi-square effect size of W=0.51 (Aim 3).

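### The MFI test is an unqualified Student's t-test on pre/post data from the same patients, which does not match the paired tests behind the Aim 1 power

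*Protocol article*

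**What the plan says.** All places are in the Protocol article.

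- **Primary aim.** The question is put per cycle and MFI is a named measure: "We will investigate whether each cycle of desensitization is effective at", with the first item "reducing antibody strength as measured by MFI and titers and" the second item lowering cPRA.
- **Antibody evaluation.** The data are before-and-after values in the same patient, for MFI, titer and cPRA alike: "We will collect samples pre and post each cycle to assess for any change in class I and class II anti-HLA abs (MFIs, titer and" (the list closes with cPRA).
- **Study regimen.** Several cycles per patient are expected, though no number is given: "We anticipate that a number of patients will need multiple cycles in order to have sequential reduction in antibodies".
- **Statistical and analytical plan.** For the effect of each cycle on cPRA, "we will fit a linear mixed model with the patient treated as a random effect to control for repeated measures". The next sentence turns to MFI: "Continuous data (MFI) will be evaluated by mean MFI for class I and class II antibodies respectively with significance determined using", and the test it names is Student's t-test, with no further qualification. A later sentence of the same paragraph names paired t-tests or Wilcoxon signed rank tests, for titers and cPRA between the last cycle and transplant and for DSA reduction. The change in MFI over a cycle is not in that list.
- **Number of subjects and sample size justification.** With 30 patients, the article claims 80% power at d = 0.53 "for analyses using paired t-tests" and at d = 0.55 for signed rank tests, both under Aim 1.

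**The concern.** MFI and cPRA come from the same samples, yet the plan acknowledges the repeated-measures structure for one and not for the other. The paragraph uses the word paired where it assigns paired tests and leaves it out for MFI, so an analyst following the text could run a two-sample test of pre against post values. That would ignore the within-patient correlation and would not be the analysis whose power is stated.

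There is a second, separate gap. Because patients may contribute several cycles, even a paired test needs a stated unit of analysis. If all cycles go into one test as if independent, the clustering that the authors handle for cPRA goes unhandled for MFI.

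The two problems act in opposite directions. Ignoring positive pre/post correlation makes the test conservative and costs power. Pooling cycles makes it too liberal. With the cohort fixed at 30, neither is easily absorbed.

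**Working it through.** **Inputs from the article:** n = 30; d = 0.53; 80% power; paired t-test. **Assumed, because the article does not give them:** two-sided alpha of 5%; pre/post correlation ρ; number of cycles pooled k; intraclass correlation (ICC) of the changes within a patient. Aim 1 is taken to be the Primary aim.

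**Step 1. Reproduce the stated power.** For the paired t-test the noncentrality is d√n = 0.53 × √30 = 2.903, with 29 degrees of freedom and critical value 2.045. Power is 80.1%, and the smallest detectable d at 80% is 0.529. For the signed rank test, with effective n = 30 × 3/π (normal data), the smallest detectable d is 0.543 and power at 0.55 is 81.1%. The article's figures are correct for paired analyses.

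**Step 2. Same data, two-sample test.** A paired effect d corresponds to a mean difference of d√(2(1 − ρ)) in units of the single-time-point SD: 0.53, 0.41 and 0.24 SD at ρ = 0.5, 0.7 and 0.9. The two-sample test takes the variance of the mean difference as 2σ²/n, whereas it really is 2σ²(1 − ρ)/n. Its statistic is therefore shrunk by about √(1 − ρ), and power is roughly Φ(2.903 − 2.002/√(1 − ρ)), where 2.002 is the critical value on 58 degrees of freedom. At ρ = 0.5 this gives Φ(2.903 − 2.831) = Φ(0.072) ≈ 53%. The approximation is poor in the far tail, so the table comes from simulation of correlated pairs (at least 40,000 replicates per cell).

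| ρ (assumed) | Paired: power | Two-sample: power | Two-sample: type I error |
|---|---|---|---|
| 0 | 80% | 81% | 5% |
| 0.3 | 80% | 69% | 2.0% |
| 0.5 | 80% | 53% | 0.7% |
| 0.7 | 80% | 25% | 0.08% |
| 0.9 | 80% | 0.4% | about 0 |

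The standard two-sample power formula must not be used here, because it assumes independent samples and understates the loss at high ρ.

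**Step 3. Paired test with cycles pooled.** If k paired differences per patient enter one t-test as independent, the variance is understated by the design effect 1 + (k − 1) × ICC. For k = 3 and ICC = 0.5 this is 1 + 2 × 0.5 = 2.0, and the type I error is roughly 2[1 − Φ(1.987/√2.0)] = 16%, where 1.987 is the critical value on 89 degrees of freedom. Simulation gives:

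| k | ICC 0.2 | ICC 0.5 |
|---|---|---|
| 2 | 7.3% | 10.8% |
| 3 | 9.7% | 16.8% |

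With one pair per patient in each test, as when each cycle is tested separately, this inflation does not arise and the error stays at 5%.

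**The case against.** The strongest defence is that the paired t-test is itself a form of Student's t-test. The article nowhere says unpaired, two-sample or independent. The sample size section cites paired tests for Aim 1, net MFI reduction is defined as a pre/post change, and the sentence on paired tests says they will also be used, which can be read as in addition to paired testing elsewhere. This stands in part: pairing may well be what was intended, and a reader who infers that the article prescribes an unpaired test goes further than the text. What remains is that the paragraph does not say paired for MFI while saying it for other comparisons, so the two sections have to be reconciled.

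A reader might also infer that individual antibodies or beads will be pooled as independent observations, with a large rise in false positives. The article does not support that. It tests mean MFI per class, which most naturally gives one value per patient, class and time point. Likewise, the Primary aim is put per cycle, so pooling over cycles is possible but not stated.

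Nor does the pairing problem point to false claims of benefit: on its own it makes the test conservative.

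It could be said that such detail belongs in a fuller document. That would hold if the article left the MFI test open, but it names one. Finally, testing a difference in means while describing a proportional reduction is common practice and is not counted as an error here.

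**Conclusion.** The point holds as an inconsistency to be resolved. The test named for a primary-aim measure is not stated to be paired and carries no patient effect, although the data are paired, cPRA from the same samples is modelled with a patient effect, and the Aim 1 power rests on paired tests.

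If the wording is taken as a two-sample test, the stated 80% power falls to about 53%, 25% and 0.4% at ρ = 0.5, 0.7 and 0.9. If a paired test is meant but two or three cycles are pooled as independent, the type I error is about 7% to 17%. If a paired test per cycle with one pair per patient is meant, the analysis is sound and only the wording is at fault. The values of ρ, k and ICC are assumptions.

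This should be fixed. It is not graver than that, because the study calls itself preliminary, MFI is one of several primary-aim measures, and the two definitions of a meaningful response under Antibody evaluation do not depend on this test.

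**What to change.** In the Statistical and analytical plan, replace the Student's t-test for MFI with the mixed model already planned for cPRA: a patient random effect, and one mean MFI per patient, HLA class and time point. At minimum, specify a paired t-test or Wilcoxon signed rank test for each cycle, with one pair per patient. Either choice removes the conflict with the sample size section, and the second matches its power figures directly.

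Optionally, analyse MFI on the log scale, so that the estimated post/pre ratio is on the same proportional footing as the net MFI reduction.

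The cost is a change of wording. No new data are needed, and the sample size figures can stay as they are.

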**Methods:**

This prospective, observational study will include about 30 patients from 6 pediatric clinical sites, an HLA core and a mechanistic core lab. Patients aged 10–24 years, highly sensitized with class I and/or class II cPRA ≥ 50% (MFI > 4000), will be included. Exclusion criteria: EBV seronegative, HIV+, and a history of hematologic malignancy. Secondary endpoints include mechanistic studies on how desensitization affects cellular subsets producing HLA Abs, whether reductions in antibody strength persist until transplant, and post-transplant outcomes such as antibody mediated rejection and graft survival.

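### Paired tests of difference, possible only in transplanted patients, cannot show that the antibody reduction is maintained up to transplant

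*Protocol article*

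**What the plan says.** The Primary aim section of the protocol article poses the question: "We will also determine whether the reduction in antibody strength is maintained with BELA between the last cycle and time of transplant". The abstract lists the same question among the secondary endpoints ("whether reductions in antibody strength persist until transplant").

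The Statistical and analytical plan names one analysis for it, paired t-tests or Wilcoxon signed rank tests to "examine whether levels of antibody titers and cPRA remain constant between the last desensitization cycle and time of transplant". The pair runs from the last cycle to transplant. The same sentence applies these tests to reductions in donor-specific antibodies (DSA), which the Primary aim ties to the crossmatch: "Reduction in DSA at the time of crossmatch will be studied to establish the functional relevance of our strategy".

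The Antibody evaluation section schedules further samples: "They will also be collected at two-week intervals during the maintenance phase". The Study regimen section indicates that maintenance begins once a patient is judged adequately desensitized. The analysis section does not assign these samples to the durability question. Its linear mixed model is for the effect of each cycle on cPRA.

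The sample size section gives 80% power to detect d = 0.53 (paired t-test) or d = 0.55 (Wilcoxon) with 30 patients. Both figures concern detecting a difference.

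**The concern.** There are two separate problems.

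- **Test and question do not match.** A non-significant paired test does not show stability. It may mean that nothing changed, or that too few pairs were available to see a change. The fewer the pairs, the easier it is to obtain a result that looks like durability. The article states no margin or interval criterion for calling levels constant.
- **The pair closes at transplant.** Patients who die waiting, are delisted or are still waiting have no second value. The Introduction says that sensitization lengthens the wait, raises waitlist mortality and limits the donor pool, so a patient whose antibodies return may be less likely to supply a pair.

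Sustained suppression is the reason given for adding belatacept: the article describes brisk rebound after carfilzomib and argues from it for combined therapy. Both problems could favour the conclusion that suppression lasted. The sample size section says the results will inform a larger study, so a mistaken conclusion would carry forward.

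**Working it through.** **Inputs.** From the article: 30 patients, 80% power, d = 0.53 for the paired t-test. Not in the article, so assumed: two-sided 5% significance, the number transplanted, the true size of rebound, and how strongly rebound affects the chance of transplant. Rebound is in SD of the paired change.

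**Step 1: reproduce the stated power.** For a paired t-test with n pairs, power = P(|T| > t(0.975; n−1)), where T is noncentral t with n−1 degrees of freedom and noncentrality d√n. With n = 30 and d = 0.53, the noncentrality is 0.53 × √30 = 2.90 and the critical value is 2.045. Power is 0.801, and the effect detectable at 80% is 0.529. The stated figure is correct. A one-sided 5% test would give 0.883, so the two-sided assumption fits.

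**Step 2: chance that a real mean rebound is non-significant.** This is 1 − power from the same formula.

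| Pairs | Rebound 0.53 SD | Rebound 0.30 SD | Half-width of 95% CI, t(0.975; n−1)/√n |
|---|---|---|---|
| 30 | 20% | 65% | 0.37 SD |
| 20 | 39% | 75% | 0.47 SD |
| 15 | 52% | 81% | 0.55 SD |

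The first row requires all 30 patients to be transplanted.

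**Step 3: illustrate the selection.** Let rebound in all patients be normal with mean 0.50 and SD 1. Let the log-odds of transplant be a − b × rebound, with b = 0.5, 1.0 or 1.5. The odds of transplant then fall by a factor of e^b = 1.6, 2.7 or 4.5 per SD of rebound. Choose a so that a given share is transplanted, and take the mean rebound in those transplanted (true value 0.50).

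| Share transplanted | 1.6-fold | 2.7-fold | 4.5-fold |
|---|---|---|---|
| 90% | 0.45 | 0.41 | 0.38 |
| 70% | 0.36 | 0.25 | 0.17 |
| 50% | 0.26 | 0.09 | −0.03 |

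Every entry is below 0.50, by between 0.05 and 0.53 SD.

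**Step 4: what a margin rule could deliver.** Suppose there is no true change, and maintenance is concluded when the upper 95% limit lies below a margin m. The chance of success is P(T > t(0.975; n−1)) with noncentrality m√n. For an assumed m = 0.5 SD this is 75%, 56% and 44% with 30, 20 and 15 pairs; 34 pairs are needed for 80%. These are figures for simple pairs. A model using repeated samples may differ.

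**The case against.** The strongest reply is that the article never says a p-value above 0.05 will be reported as constant. It says the tests will examine the question, and a paired test is a fair way to detect rebound. That is right. A reader might infer that durability will be declared from non-significance, but the text does not say so, and the miss rates in Step 2 apply only if results are read that way. What stands is that no test capable of supporting maintenance is named.

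The 20% at 30 pairs is simply the planned type II error. The higher figures depend on assumed numbers transplanted. This also stands.

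A reader might infer that DSA are bound to look reduced because donors are accepted only once the antibodies against them are low. The article does not support that: it discusses transplant across a positive crossmatch and plans outcomes with and without one. A patient who rebounds may therefore be transplanted and contribute a pair. The direction of the selection is plausible, but its size is unknown.

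A reader might also take the two-weekly samples to cover every enrolled patient. They are scheduled for the maintenance phase only. For patients who never reach it, the article schedules samples before and after each cycle.

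Finally, a numeric margin and rules for death or delisting often belong in a SAP, which is not shown, and the Antibody evaluation section does say that cPRA will be assessed at different time points. The study is described as preliminary, and its modest size is acknowledged. These points limit the criticism to what the article itself fixes: the test and the two ends of the pair.

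**Conclusion.** The point holds in a limited form. The stated analysis can detect rebound among transplanted patients. It cannot show maintenance, and it leaves out everyone who does not reach transplant.

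At the rebound the study is sized to detect (0.53 SD), reading non-significance as constancy would be wrong in 20% of studies in the best case, and in 39% to 52% with 20 to 15 pairs. Those numbers of pairs and the two-sided 5% level are assumptions.

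That untransplanted patients supply no pair is certain. That this biases the observed rebound towards zero holds if rebound lowers the chance of transplant, which the article's own account makes plausible. The size cannot be derived from the documents: over the assumptions tried, a true 0.50 SD appears as anything from −0.03 to 0.45 SD. The documents do not support the stronger claim that real rebound will often be reported as constant, because they give neither a reporting rule, nor a transplant rate, nor an expected rebound.

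**What to change.** Replace the durability test in the Statistical and analytical plan as follows.

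- Fit the patient-level mixed model to all samples taken after the last cycle, including the two-weekly maintenance samples, from every patient who enters maintenance, whether or not transplanted. Time since the last cycle is the term of interest.
- Report mean rebound with a 95% confidence interval. Conclude that the reduction was maintained only if the upper limit lies below a margin fixed before analysis, for example one four-fold titer step and a stated number of cPRA points. Otherwise report that maintenance was not shown.
- Report how many patients were transplanted, died, were delisted or are still waiting. State that the model reduces but does not remove informative dropout, since follow-up still ends at these events.
- Present DSA change as applying to transplanted patients only, beside the change in all antibodies that exceeded 4000 MFI before cycle 1.

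The cost is a change of analysis text and agreement on a margin. The maintenance samples are already scheduled for the patients concerned. The downside is that so small a study may be unable to claim maintenance even if there is no rebound.
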